## Abstract

**Background:**

Renal replacement therapy (RRT) is usually indicated for patients with chronic kidney disease (CKD) with glomerular filtration rate below 10 ml/ml/min/1.73m^2^. However, the need for RRT and timing of dialysis initiation are debatable for patients aged 70 years or older. We here describe the study design and methodology of the Aging Nephropathy Study (AGNES) protocol that aims at evaluating to what extent geriatric-related conditions such as frailty, cognitive dysfunction, and presence of comorbidities have an impact on survival and RRT initiation in this group of patients. In this manuscript we provide detailed information about the AGNES study design and methodology.

**Methods:**

AGNES is a prospective observational cohort that aim to investigate clinical, biochemical and demographic factors associated with RRT initiation and mortality of patients with CKD stage 4 or 5 who are aged 70 years and older. We plan to include 200 patients over 5 years. Clinically stable outpatients on conservative management for at least 6 months will be recruited from the Nephrogeriatric Clinic at the *Hospital das Clinicas da Universidade de Sao Paulo*, Brazil. Eligible patients are submitted to a full clinical examination, geriatric assessment, and blood test at baseline. Following the baseline visit the patients are being monitored during an observational follow up period of at least 12 months during which patients will be contacted in the clinic at their regular follow up or by phone until either RRT initiation or death occurs. This cohort includes evaluation of cognition by the education-adjusted 10-point Cognitive Screener (10-CS), frailty by Fried index score, a complete nutritional assessment (by body composition assessment, global subjective assessment and dietary intake), comorbidities by Charlson comorbidity index and biochemical markers including FGF-23 and Klotho.

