## Methods

### Primary hypotheses

Our primary hypothesis is that mortality is associated with greater number of comorbidities and with a high impact of geriatric issues. The decision of beginning RRT will be more likely to occur in patients with fewer burdens of geriatric syndromes.

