### Follow up

After a baseline visit, patients will be followed by telephone contact every 4 months to check mortality and the beginning of RRT. The follow up will last at least 12 months. In addition, patients will be routinely followed in the same outpatient clinic with an average interval between visits of 4 to 5 months. Patients can withdraw their consent to participate in the study at any time.

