### Statistical analysis

First, we will perform a descriptive analysis of the demographic, nutritional and clinical parameters of the included patients. Specific data includes geriatric syndromes, full nutritional assessments, muscle strength (based on HGS), body composition, sleep questionnaires, CCI, and non-invasive hemodynamic parameters. Continuous data will be presented as mean ± SD and categorical data will be presented as proportion. Normality distribution will be tested by D’Agostino omnibus test. Patients will be classified according to clinical evaluation according to the cognitive deficit, frailty, nutrition status, stage of renal function (4 or 5) and the presence of sleepiness and poor quality of sleep. Exploratory analyses will include an association between any of the above-mentioned clinical diagnoses with the 2 outcomes: death or beginning of renal replacement therapy. These outcomes will be closely monitored by the study team in the routine visits or and/or by telephone contact. A *p* value < 0.05 will be considered significant. Analyses will be performed using SPSS 22.0 (SPSS Inc., Chicago, IL, USA) and *GraphPad Prism® software* (GraphPad Software, Inc., CA, USA).

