The results and interpretation of this study should consider some limitations: first, as this is not a large multicenter study the number of patients is relatively know. Second, polysomnography will be available only for a subset of patients. Third, the choice of starting renal replacement therapy is a shared-decision and many factors not investigated within the study such as family and social support may bias this outcome. However, we aim for a real-world study that likely will mimic the usual clinical practice, and considering that it is unethical to randomize patients to start dialysis or not regardless of their wishes, the current design is the one achievable.

In summary, this clinical study intends to address a common challenging situation in renal care of elderly individuals with CKD namely the choice between initiating renal replacement therapy vs. continue with conservative management. One of many questions we hope to answer is: Who are at higher risk of death when initiating dialysis in elderly patients and in whom would conservative management be more appropriate? However, we will evaluate not only survival benefits but also patient-reported outcomes including parameters related to health benefits and quality of life. The identification of features associated with patient survival, health benefits and quality of life may inform treatment strategies for better management of elderly patients with CKD. Ultimately, this study will address what, for whom and when considering a given treatment for individuals of the same age but with different functional state will result in opposite outcome.

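### The Abstract ends contact at RRT initiation but the Follow up section does not; if the Abstract governs, deaths after dialysis start go unrecorded and overall mortality cannot be analysed

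*Protocol article*

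**What the plan says.** **When contact ends.** The Abstract (Methods) gives a follow-up period of at least 12 months and, in the same sentence, says that "patients will be contacted in the clinic at their regular follow up or by phone until either RRT initiation or death occurs". No other statement in the article says when contact stops. The Follow up section says that "patients will be followed by telephone contact every 4 months to check mortality and the beginning of RRT" and that "The follow up will last at least 12 months". It adds routine clinic visits, and it neither ends the calls at RRT nor says that they go on afterwards.

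**What the data are for.** The primary hypothesis is that "mortality is associated with greater number of comorbidities and with a high impact of geriatric issues"; it is not limited to death before RRT. Its second half is that "The decision of beginning RRT will be more likely to occur in patients with fewer burdens of geriatric syndromes". The Statistical analysis section links baseline diagnoses "with the 2 outcomes: death or beginning of renal replacement therapy" and does not say how one outcome is handled when the other comes first. Among the questions that the Discussion hopes to answer is: "Who are at higher risk of death when initiating dialysis in elderly patients and in whom would conservative management be more appropriate".

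**The concern.** RRT initiation is both an outcome and, in the Abstract, the point at which contact ends. A patient who starts dialysis and then dies would count as an RRT event, and the death would not be seen. The Background describes the risk of death in elderly dialysis starters as very high in absolute terms, so the unobserved period is one in which many deaths are expected.

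Two things are at stake. First, the mortality hypothesis would in practice be tested on a narrower outcome, death before RRT. Second, the Discussion's question about dialysis starters needs survival after dialysis begins, and there would be no such data. The choice of model can be left to an analysis plan, but no analysis can recover deaths that were never ascertained.

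**Working it through.** **1. The passages side by side**

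| Patient | Abstract rule | Follow up section |
|---|---|---|
| Starts RRT at month 3 | Contact ends at month 3 | Mortality checks to at least month 12, if the minimum applies to RRT starters |
| Starts RRT at month 11 | Contact ends at month 11 | Only 12 − 11 = 1 month after RRT is assured |
| Starts RRT after month 12 | Contact ends at RRT | Nothing after RRT is assured |

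The two sections give different observation periods. Even the more generous one guarantees little time after RRT, because its minimum runs from baseline and not from dialysis start.

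**2. The plan's own event count**

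The Power analysis section gives 197 individuals or 119 events. It states no effect size and no exposure split, and it does not say whether an event is death, RRT or either. The figure therefore cannot be reproduced, and it cannot show whether deaths after RRT were counted on. It is not used below.

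**3. Deaths missed if contact ends at RRT**

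Inputs:
- 200 patients (Abstract).
- Mortality after dialysis start of 22.5% at 30 days, 44.2% at 180 days and 54.5% at 365 days. These come from the study of patients aged 65 and over that the Background cites.
- RRT uptake p. The article does not give it, so 10–50% is assumed.

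Formula: missed deaths = 200 × p × mortality after dialysis start.

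| Uptake p | RRT starters | Missed by 30 days | Missed by 180 days | Missed by 365 days |
|---|---|---|---|---|
| 10% | 20 | 4.5 | 8.8 | 10.9 |
| 20% | 40 | 9.0 | 17.7 | 21.8 |
| 30% | 60 | 13.5 | 26.5 | 32.7 |
| 40% | 80 | 18.0 | 35.4 | 43.6 |
| 50% | 100 | 22.5 | 44.2 | 54.5 |

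The first-year loss is about 11 to 55 deaths. This is probably an upper range, for three reasons:
- The cohort consists of clinically stable outpatients, and patients with a life expectancy under 6 months are excluded.
- RRT starters are expected to carry less geriatric burden.
- Some patients will start RRT less than a year before any closing date.

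If the one-year mortality were half the cited figure (0.545 / 2 = 0.2725), the range would be 200 × 0.10 × 0.2725 = 5.5 to 200 × 0.50 × 0.2725 = 27.3.

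**4. Why the loss is not evenly spread**

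The primary hypothesis expects more RRT where burden is lower. As an illustration, assume 100 low-burden patients with 40% uptake, 100 high-burden patients with 20% uptake, and the same post-dialysis mortality in both groups:
- low burden: 100 × 0.40 × 0.545 = 21.8 first-year deaths missed;
- high burden: 100 × 0.20 × 0.545 = 10.9 missed.

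Twice as many deaths would drop out of the low-burden group. Higher post-dialysis mortality in the high-burden group would narrow or reverse this difference. In general, though, the association of burden with death before RRT need not match its association with all-cause death.

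**The case against.** **The stop at RRT stands only in the Abstract.** A reader might infer that the design is fixed and that nobody is observed after dialysis starts. The documents do not support that. The Follow up section has mortality checks, a 12-month minimum and routine visits, with no stated exception for RRT starters. This objection stands: the defect is a conflict between sections, and the loss is conditional on the Abstract being followed. It does not dispose of the point. The Abstract puts the same 12-month minimum beside the stop, so the minimum does not clearly override it, and the Follow up section never says that calls continue after RRT.

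**Ending observation at RRT can be legitimate.** A reader might infer that censoring at RRT biases every mortality analysis. It does not. The cause-specific hazard of death before RRT, with RRT as a competing event, is a coherent target, and the Abstract's own discussion speaks of patients not yet on dialysis. A gap between that association and the one for all-cause death is a difference in what is estimated, not in itself censoring bias. The dependence of RRT on burden, and the Discussion's admission that "many factors not investigated within the study such as family and social support may bias this outcome", matter if death before RRT is read as overall mortality or as mortality had RRT not occurred. The handling of competing events may also be set out in a full analysis plan that is not shown. All of this stands. What remains is that the primary hypothesis speaks of mortality without restriction.

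**The question about dialysis starters is not a central aim.** The Discussion offers it as one of many, and it appears in neither the primary nor the exploratory hypotheses. That also stands, so it should not be treated as the study's main question. It is still a stated aim that needs data after RRT.

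**The cited mortality may not transfer.** Agreed; the count is presented as an upper range.

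**Conclusion.** The point holds as an inconsistency with a material consequence. The Abstract and the Follow up section disagree on whether patients are observed after RRT starts. If the Abstract governs, the study can analyse death before RRT but not the overall mortality of its primary hypothesis, and it cannot answer the Discussion's question about risk of death on starting dialysis.

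The size is about 11 to 55 missed first-year deaths per 200 patients. This rests on the cited 54.5% one-year mortality, which is probably too high for this cohort, and on an assumed RRT uptake of 10–50%. If the Follow up section governs and its minimum applies to RRT starters, some of these deaths would be recorded, with certainty only to month 12 from baseline. The documents do not allow an estimate of how far the association with geriatric burden would shift, so no figure is given for that.

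**What to change.** Reconcile the Abstract, the Follow up section and the Discussion:

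- **Ascertainment.** State that the existing four-monthly calls continue for vital status after RRT start, for every patient, to a common closing date.
- **Mortality outcome.** Analyse all-cause death from baseline. Report death before RRT as a separate cause-specific analysis with RRT as a competing event.
- **Question about starting dialysis.** Analyse survival from RRT start, or treat RRT as a time-dependent covariate.
- **If calls are not continued.** Restate the mortality outcome as death before RRT throughout, and delete the Discussion's claim about risk of death on starting dialysis.

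The cost is a few short calls per RRT starter, at most 12 / 4 = 3 a year on the present schedule, and a sentence or two in the protocol. Recruitment has begun, so the rule should be settled now, while vital status can still be collected prospectively.

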**Discussion:**

The AGNES cohort, a real-world study of current clinical practice in elderly patients with advanced CKD prior to dialysis initiation, will shed light into progression of CKD and its complications, indications of RRT and factors determining survival. This investigation will elucidate to what extent geriatric conditions, nutritional status and clinical factors are associated with survival, quality of life and RRT initiation in elderly CKD patients not yet on dialysis.

**Trial registration:**

Registered on ClinicalTrials.gov on 18 October 2019 (NCT04132492).

## Background

Chronic kidney disease (CKD) is a common clinical condition in elderly individuals and is associated with large morbidity and mortality. The high prevalence of hypertension and diabetes in the aging population partially explains the high burden of CKD in the elderly population because these two conditions are among the most common causes of CKD.

Considering the KDIGO classification of CKD, the overall prevalence of patients with CKD stage 5 CKD (estimated glomerular filtration rate - eGFR < 15 ml/ml/min/1.73m^2^) is much higher in elderly individuals [1]. Assessment of eGFR is now a common practice that has replaced creatinine clearance measurements in the clinical practice; however, it is not clear which is the best equation for eGFR calculation in elderly patients especially in those with advanced CKD. Whereas the CKD-EPI creatinine-based eGFR overestimates the true GFR in this population, eGFR calculated by the CKD-EPI cystatin C formula is described to be better for older individuals, and the equation derived from the Berlin initiative study (BIS-1) also seems to be reliable for use in stages 1–3 CKD. Recently, a study tested these equations against the gold-standard inulin clearance and concluded that none of them was superior in estimating GFR in elderly individuals [2].

Managing CKD in the elderly is challenging and it is not always clear if dialysis initiation will provide a survival or health benefit. Thus, the best approach considering the choice of conservative care vs. renal replacement therapy (RRT) is still debatable. This is mainly because there is still limited information about these issues and specific evidence-based guidelines for elderly patients with CKD are lacking. However it is evident that geriatric issues such as frailty, cognition, and treatment complications must be taken into account in the shared decision making process when choosing between conservative treatment and RRT. There is a general belief that the *relative risk of mortality* associated with low eGFR is smaller in elderly patients than in younger individuals. However, elderly patients starting on dialysis has a very high *absolute risk of death* that associates with baseline diseases, sleep disorders, and deteriorated functional status and other complications. Indeed, a recent study showed that the mortality rate among patients 65 years and older was 22.5% at 30 days after starting dialysis, 44.2% at 180 days, and 54.5% at 365 days [3]. In addition, factors affecting life quality such as functional status may deteriorate as well. In a study based on a national registry of patients undergoing dialysis in the United States of America, initiation of dialysis among nursing home residents with an average age of 73 years old was associated with a substantial and sustained decline in functional status [4].

Considering the above mentioned, this study will enrol elderly patients (70 years and older) with stage 4 and 5 CKD under conservative management as an attempt to identify clinical, demographic and biochemical factors associated with mortality and the initiation of RRT, considering the presence of comorbidities and geriatric conditions.

## Methods

### Primary hypotheses

Our primary hypothesis is that mortality is associated with greater number of comorbidities and with a high impact of geriatric issues. The decision of beginning RRT will be more likely to occur in patients with fewer burdens of geriatric syndromes.

### Exploratory hypotheses

Frailty and cognition deficit will be associated with high mortality rate;Presence of comorbidities, in particular diabetes and congestive cardiac failure will be associated with mortality and beginning of RRT;Klotho and Fibroblast growth factor (FGF-23) will be associated with both outcomes, mortality and beginning of RRT;Protein energy wasting and sarcopenia nutritional status will be associated with high mortality rate;Sleep disorders, particularly poor sleep quality, will be associated with mortality.

### General study design

AGNES was designed as a prospective unblinded cohort from a single academic center, evaluating risk factors of mortality and biomarkers associated with beginning of RRT. Patients who agree to participate are signing the written informed consent. Baseline data are collected in the same day.

### Ethical consideration

The AGNES was registered at clinicaltrials.gov (#NCT04132492). It is conducted in accordance with the Declaration of Helsinki. The Local Board Ethical Committee has approved the protocol (*Comissão de Ética para Análise de Projetos de Pesquisa do HCFMUSP*, application 97,812,918.3.0000.0068, number 3.438.278). Patients are providing written informed consent before their enrollment in the study. In order to maintain confidentiality, the investigators deidentified the health information.

### Setting

Patients are being recruited from the Nephrogeriatric outpatient clinic at the *Hospital das Clinicas, Universidade de Sao Paulo*, Brazil, which adopts a multidisciplinary approach and team. The team includes dietitian, nurse, nephrologist, and geriatric physician.

#### Inclusion criteria

Patients aged 70 years old or older, both sexes, with CKD stage 4 or 5 according to eGFR calculated by the CKD-EPI formula;

#### Exclusion criterion

Patients with life expectancy lower than 6 months according to the investigator’s judgment; patients with untreatable cancer.

### Study visit procedures

Potential candidates for the AGNES study are being invited by the investigator and screened for eligibility. Eligible patients are being approached for recruitment. After review of study procedures, risks and benefits, those who agreed and signed the informed consent form are included. Blood sample is collected in the same visit to biorepository.

Baseline parameters recorded include: global geriatric assessment (GGA) performed with the supervision of the geriatric physician, demographic and clinical history, medications in use, nutritional assessment, questionnaires for sleep disorders, non-invasive hemodynamic monitoring and body composition assessment by bioelectrical impedance (BIA).

### Global geriatric assessment (GGA)

All participants are being submitted to a GGA at baseline, performed by the same physician. GGA includes a structured interview, physical examination, and a geriatric functional assessment. Geriatric domains assessed are functional status (daily life activities), nutritional status, physical health, cognition, depression, and social and family support [5].

The Katz Index of Independence in Activities of Daily Living (ADL) [6], validated to the Portuguese language [7] will be used to assess the functional status. The Katz index of ADL provides measures independence and need of assistance during bathing, dressing, toileting, transferring, continence, and feeding. Higher scores indicate more patient independence.

The Geriatric Depression Scale (GDS)-Short Form will be used to identify presence of depression and its severity [8]. This test yield scores that range from 0 to 15 with higher scores indicating higher depression probability.

The education-adjusted 10-point Cognitive Screener (10-CS) [9] assesses cognitive performance. Individuals with scores ≥8 are considered to have normal or near-normal cognition.

### Frailty index

Frailty is being evaluated using criteria established by Fried et al. [10], with 5 components as following:
Unintentional weight loss ≥5% of body mass in the last year;Weakness (loss of palmar prehension force), adjusted for age and body mass index (BMI).Exhaustion (audited information based on two questions from Center for Epidemiological Studies Depression (CES-D) scale; a score from 1 [fatigue or exhaustion felt rarely or not at all] to 4 [fatigue or exhaustion felt most of the time], 3 or 4 points means that the test is positive for decreased physical activity);Slow gait speed (walking time over a distance of 4.6 m); interpretation of results takes into account sex and height;Low physical activity (measured by weekly energy expenditure in kcal, based on self-report of specific physical activities and exercises performed according to validated questionnaires such as the IPAC - International Physical Activity Questionnaire validated to Portuguese)

Patients who fulfilled none of the criteria are considered non-fragile, patients who fulfilled 1 and 2 criteria are classified as pre-fragile, and patients who fulfilled 3 or more criteria are classified as fragile.

### Follow up

After a baseline visit, patients will be followed by telephone contact every 4 months to check mortality and the beginning of RRT. The follow up will last at least 12 months. In addition, patients will be routinely followed in the same outpatient clinic with an average interval between visits of 4 to 5 months. Patients can withdraw their consent to participate in the study at any time.

